### Interim analyses {21b}

Interim analyses will be conducted to examine initial trial efficacy and safety outcomes. Frequencies (percentages), means (standard deviations), or medians (interquartile ranges) will be used to summarise the data collected from questionnaires and surveys. Statistical tests will be performed, e.g. Chi-square or Fisher’s exact test for categorical variables, and two independent sample *t*-tests or ANOVA for continuous variables. Nonparametric tests will be used as deemed fit. For binary outcomes, the strength of associations between independent and dependent variables will be assessed by odds ratio estimated in logistic regression models. Crude associations will be evaluated using univariate models. Subsequently, associations will be evaluated using multivariable models adjusted for potential confounders.

### Methods for additional analyses (e.g. subgroup analyses) {20b}

We will carry out additional analyses that evaluate the effect of the intervention on the children born to the women during the GDM pregnancy with a focus on cognitive and socio-emotional development (ASQ-3, BASC-3-BESS, BRIEF, StimQ) and sleep (BISQ-R-SF, CSHQ) using linear mixed models (LMM) with outcome measurements (baseline and the three follow-up time points) based on intention-to-treat (ITT).

Descriptive statistics will be used to establish the intervention response rate based on the number of coaching sessions completed, logins into the App, and estimated time spent.

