### Eligibility criteria {10}

All eligible females in this study will be (a) women between 21 and 45 years old; (b) with a history of GDM (at least 1 year and no more than 10 years); (c) Chinese, Malay, or Indian ethnicity; (d) BMI between 18.5 and 35 kg/m^2^; (e) not planning to conceive in the next 1 year; (f) not performing exclusive breastfeeding during the study period; (g) owners of a smartphone compatible with the study mobile Apps; (h) proficient in the English language; (j)willing to comply with study protocol; and (k) able to provide written informed consent.

Exclusion criteria include (a) current or previous diagnosis of diabetes (type 1 or 2), except GDM; (b) currently pregnant; (c)given birth within the last 12 weeks; (d) severely limited mobility (e.g. wheelchair-bound, require long-term walking aid, etc.); (e) diagnosed with malnutrition or eating disorder; (f) diagnosed with cancers, unstable heart diseases, severe kidney disease, severe liver disease; (g) diagnosed with severe insomnia, unstable mental conditions, dementia, or cognitive impairment; (h) experienced alcohol or drug abuse; (i) currently having medications known to influence glucose metabolism (e.g. peroral corticosteroids); and (j) currently participating in a concurrent clinical trial or lifestyle intervention study.

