*Ages & Stages Questionnaires-3* (*ASQ-3*) (1–66 months): The ASQ-3 development screening tool assesses children’s communication, autonomy, compliance, adaptive functioning, affect, and interaction with people. ASQ-3 is a reliable and valid instrument with a test–retest reliability of 92%, a sensitivity of 87.4% and a specificity of 95.7% [55].

*Behaviour Rating Inventory of Executive Functions-2 (BRIEF-2) parent form*: BRIEF-2 is designed for use in medical and educational settings to estimate the global executive function of children/youth and determine whether a comprehensive assessment is appropriate (age 5–18 years). BRIEF-2 has shown reliability coefficients ranging between 0.8 and 0.9 [56].

*Behavioural and Emotional Screening System (BASC-3-BESS) Parent Form*: This screens children and adolescents’ behavioural and emotional strengths and weaknesses (age 3–18 years 11 months). BASC-3 BESS has high internal consistency at 0.80 [57].

Changes in the child’s sleep will be assessed at the baseline visit and the first-year visit. The following is a description of child sleep questionnaires:

*The Brief Infant Sleep Questionnaire-Revised Short Form* (*BISQ-R-SF*): A parent-reported toddler (0–3 years) sleep over the prior 1 week, assessing sleep patterns, ecology, and parental perceptions of sleep. The BISQ-R indicates excellent reliability at 0.80 [58].

*Children’s Sleep Habits Questionnaire (CSHQ) Short Form (SF)version*: The SF-CSHQ assesses the frequency of children’s behaviours associated with common paediatric sleep difficulties for children between 48 and 72 months. The SF-CSHQ has been validated, showing Internal consistency coefficients ranging from 0.90 to 0.94 [59].

After completing the 1-year RCT period, both groups will be followed up for 3 years. During the follow-up visits, body measurements, OGTT, bio-sampling, and data collection will be conducted, and the questionnaires listed above.

Additionally, the intervention group will also complete the following questionnaires through the LvL UP App:

*Patient Health Questionnaire-4* (*PHQ-4*): A 4-item self-report measure that assesses anxiety and depression symptoms. Each item is scored on a 4-point scale (0–3), and scores range from 0 to 27. The score can be used to describe a patient’s symptoms in one of the five categories: none (0–2), mild (3–5), moderate (6–8), and severe (9–12), The PHQ-4 has been shown to have good internal reliability (Cronbach alpha = 0.82) [38].

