### Participants timeline {13}

The participants’ flow for the trial is outlined in Fig. 1. Once participants are identified through one of the recruiting methods, they will be invited to the SICS clinic for screening, in which a consent form will be explained and signed, and OGTT test, height, weight, blood pressure measures, HbA1c (finger proc test) and sociodemographic survey will be completed. Those who are eligible will be randomised to one of the two arms (comparison or intervention group) and will subsequently be asked to take follow-up height, weight and blood pressure measurements, BIA, report the child’s height and weight, fasting blood draw, collection of the buccal swab, saliva, and stool sample, and complete questionnaires for the mother and their child at midpoint (26/27 weeks) visit, and year one visit after randomisation. After the midpoint assessments, additional interventions will be delivered via the HAPPY App to subjects in the intervention group who require further recommendations to improve their BMI or manage their body weight. During the 3 year-followed-up periods, participants will be asked to complete the following: (a) OGTT test; (b) height, weight and blood pressure measurements; (c) BIA; (d) fasting blood draw; (e) collection of the buccal swab, saliva and stool samples; (f) reported child’s height and weight; (g) complete mother and child questionnaires; (h) issue of Oura Ring (8 weeks); and (i) 14-day e-Diary recording in year 2, 3 and 4 visit. The schedule of enrolment, intervention, and assessments for the trial is outlined in Fig. 2.

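### The mixed model planned for the child outcomes does not match the child visit schedule: child sleep has one scheduled follow-up, not three, and the place of year 1 is unclear for the development scales

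*Protocol article*

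**What the plan says.** Methods for additional analyses {20b} of the protocol article assigns one method to all child outcomes. The effect on the children is to be evaluated "using linear mixed models (LMM) with outcome measurements (baseline and the three follow-up time points"). The instruments are listed there as "ASQ-3, BASC-3-BESS, BRIEF, StimQ) and sleep (BISQ-R-SF, CSHQ").

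The schedule is given in several places:

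- **Child sleep, text.** Outcomes {12} says that the child's "sleep will be assessed at the baseline visit and the first-year visit". Table 1 agrees.
- **Child development, Table 1.** ASQ-3, StimQ, BRIEF-2 and BASC-3-BESS are marked at baseline and at years 1, 2, 3 and 4.
- **General statements.** Outcomes {12}, directly after the child sleep scales, says that the questionnaires already described are also collected in the follow-up years. Participants timeline {13} lists "g) complete mother and child questionnaires" for years 2 to 4. Neither excepts sleep. The timeline section also places child questionnaires at the midpoint visit, where Table 1 has none.

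Age limits are given in Outcomes {12}. BISQ-R-SF is described as "A parent-reported toddler (0–3 years) sleep over the prior 1 week", and CSHQ is "for children between 48 and 72 months". ASQ-3 is limited to "1–66 months): The ASQ-3 development screening tool". StimQ runs from 12 to 72 months, BRIEF-2 from 5 to 18 years, and BASC-3-BESS from 3 years to just under 19. Only children of a GDM pregnancy count, and Eligibility criteria {10} requires women "with a history of GDM (at least 1 year and no more than 10 years").

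The only model terms stated, under {20c}, are time, group, their interaction and a random individual effect.

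**The concern.** A plan that names four occasions (baseline plus three) for every child instrument should find four occasions in the schedule. In Table 1 it finds two for sleep and five for development. The analyst would then have to decide after data collection which visits enter the model. For the development scales, that includes deciding whether the visit at the end of the randomised intervention counts.

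The age limits add a second difficulty for sleep. The two sleep scales cover separate age bands, so a child can leave one before the year-1 visit, or enter the other after baseline. Few children may have the same sleep score twice. A report by intention to treat that did not say so would suggest that the result speaks for all randomised families. Effects on children are part of Objective 2.

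**Working it through.** **Step 1: count the occasions.**

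| Instruments | Stated in {20b} | Scheduled in Table 1 |
|---|---|---|
| BISQ-R-SF, CSHQ | 1 + 3 = 4 | 1 + 1 = 2 |
| ASQ-3, StimQ, BRIEF-2, BASC-3-BESS | 1 + 3 = 4 | 1 + 4 = 5 |

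The stated four is not reproduced for any instrument. If the three follow-ups are taken to be years 2, 3 and 4, the development scales have those visits but year 1 is dropped. On the Table 1 schedule no reading fits child sleep.

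**Step 2: how many children can have a repeated sleep score.** The article does not give the children's ages. As an assumption, take age at baseline as uniform over 12 to 120 months, from the 1-to-10-year GDM window. That range is 108 months wide.

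- BISQ-R-SF at both visits, scale ending at 36 months: baseline age 12 to 24 months, 12/108 = 11%.
- BISQ-R-SF at both visits, if 0 to 3 years includes three-year-olds (to 48 months): baseline age 12 to 36 months, 24/108 = 22%.
- CSHQ at both visits: baseline age 48 to 60 months, 12/108 = 11%.

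With 400 women and one child each (also an assumption), 11% is about 44 children, or about 22 per arm.

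**Step 3: other age mixes.**

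| Assumed age at baseline (years) | BISQ-R-SF twice (to 36 months) | BISQ-R-SF twice (to 48 months) | CSHQ twice |
|---|---|---|---|
| Uniform 1–10 | 12/108 = 11% | 24/108 = 22% | 12/108 = 11% |
| Uniform 1–6 | 12/60 = 20% | 24/60 = 40% | 12/60 = 20% |
| Uniform 1–4 | 12/36 = 33% | 24/36 = 67% | 0% |
| Uniform 5–10 | 0% | 0% | 0% |
| Declining triangular 1–10 | 1 − (8/9)² = 21% | 1 − (7/9)² = 40% | (6/9)² − (5/9)² = 14% |

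With BISQ-R-SF ending at 36 months, the ranges are 0 to 33% for BISQ-R-SF and 0 to 20% for CSHQ. The wider reading of the BISQ-R-SF limit raises its upper end to 67%, but only if all the children are under four at baseline.

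**Step 4: the development scales.** Share in range at two or more scheduled visits, uniform 1 to 10 years:

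- ASQ-3: baseline age up to 54 months, 42/108 = 39%.
- StimQ: up to 60 months, 48/108 = 44%.
- BRIEF-2: 24 months or over, 96/108 = 89%.
- BASC-3-BESS: all children, 100%.

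Over the other age mixes, ASQ-3 and StimQ run from 0 to 100%, BRIEF-2 from 67 to 100%, and BASC-3-BESS stays at 100%.

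**Step 5: can a mixed model be fitted at all?** Scores were simulated for 400 children (uniform 1 to 10 years, one run), and a random-intercept model with time, group and their interaction was fitted under the age limits. It converged for all six instruments. For BISQ-R-SF, 92 children contributed, 48 of them with a repeat; for CSHQ, 118 and 30. The sleep models had two time levels.

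**The case against.** **Three may mean years 2 to 4.** Table 1 labels exactly those three visits as follow-up. This is a fair reading for the development scales, so three is not certainly a miscount. It still leaves out year 1.

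**Sleep may continue after year 1.** The general statements point that way, and Table 1 is not beyond doubt: as extracted, it has no year-1 OGTT, which the text of Outcomes {12} includes. This is why the passages need reconciling rather than one being declared right. The specific sentence on child sleep and Table 1 agree with each other, however, and are the stronger evidence. Continuing would also not give any one child the full series. Taking children as at least 12 months old at baseline, none can be within the BISQ-R-SF or CSHQ range at baseline and at all of years 2 to 4.

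**Much of the detail belongs in an analysis plan.** This is true of scoring rules, age standardisation and clustering by mother, which are not asked for here. The number of occasions is different, because the article states it and its own schedule contradicts it.

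A reader might also draw three stronger conclusions, which the documents do not support:

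- *That the mixed model cannot be fitted to the child data.* Mixed models accept unbalanced and two-occasion data (step 5). What fails is the stated three-follow-up analysis of sleep.
- *That most children cannot repeat the questionnaires.* This is untrue of BRIEF-2 and BASC-3-BESS. For ASQ-3 and StimQ it depends on an age mix that the article does not give.
- *That the comparison of arms is biased.* A child's age is fixed before randomisation, so age-eligible children in the two arms remain a randomised comparison.

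**Conclusion.** The concern holds in limited form. The analysis stated in {20b} does not match the child schedule: for sleep it cannot be run on the two occasions that Outcomes {12} and Table 1 give, and for the development scales it leaves the role of year 1 open. Repeated child sleep scores are likely to be few: about 11% of children for each scale under a uniform age of 1 to 10 years, or 22% for BISQ-R-SF if three-year-olds count. These percentages rest on assumed ages and on taking time since GDM as the child's age. The consequence is lower precision and results that describe a narrower group of children. These are additional analyses, and the conclusion on diabetes onset is untouched.

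**What to change.** 1. Reconcile Table 1, the text of Outcomes {12}, Participants timeline {13} and {20b} on which child questionnaires are given at which visits, including the midpoint and years 2 to 4 for sleep.
2. If Table 1 stands, restate {20b} in two parts. For BISQ-R-SF and CSHQ, compare the arms at year 1, with either a two-occasion model or a baseline-adjusted comparison. For ASQ-3, StimQ, BRIEF-2 and BASC-3-BESS, use a mixed model that includes year 1 as well as years 2 to 4.
3. Add child age as a covariate in both. It is already collected in the screening survey (Table 2), and the terms listed in {20c} do not include it. The purpose is precision.
4. Describe the child results as applying to age-eligible children, and report their number by arm for each instrument.

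The cost is rewording, with no new data collection if Table 1 stands. The downside is a smaller stated child sample and more modest claims for an additional analysis.

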### Methods in analysis to handle protocol non-adherence and any statistical methods to handle missing data {20c}

Intention-to-treat analysis will be used to examine trial efficacy. Total scores will be modelled using fixed effects of time, intervention group, interaction between time and intervention group, and a random effect of individual.

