**Methods:**

The study consists of a 1-year randomised controlled trial (RCT) with a 3-year follow-up period. Post-GDM women with no current diabetes diagnosis and not planning to become pregnant will be eligible for the study. In addition, participants will complete mental well-being questionnaires (e.g. depression, anxiety, sleep) and their child’s socio-emotional and cognitive development. The participants will be randomised to either Group 1 (Intervention) or Group 2 (comparison). The intervention group will receive the “LVL UP App”, a smartphone-based, conversational agent-delivered holistic lifestyle intervention focused on three pillars: Move More (PA), Eat Well (Diet), and Stress Less (mental wellbeing). The intervention consists of health literacy and psychoeducational coaching sessions, daily “Life Hacks” (healthy activity suggestions), slow-paced breathing exercises, a step tracker (including brisk steps), a low-burden food diary, and a journaling tool. Women from both groups will be provided with an Oura ring for tracking physical activity, sleep, and heart rate variability (a proxy for stress), and the “HAPPY App”, a mHealth app which provides health promotion information about PA, diet, sleep, and mental wellbeing, as well as display body mass index, blood pressure, and results from the oral glucose tolerance tests. Short-term aggregate effects will be assessed at 26/27 weeks (midpoint) and a 1-year visit, followed by a 2, 3, and 4-year follow-up period.

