### Outcomes {12}

Table 1 shows the outcomes and timeline of the study. The primary outcome will be the onset of T2D/confirmed by a 2-h 75 g oral glucose tolerance test (OGTT) over a 4-year study period. OGTT will be done at the screening visit, year 1 visit, and follow-up visits in years 2, 3, and 4. Secondary outcomes include (a) onset of impaired fasting glucose and impaired glucose tolerance; (b) changes in cardiometabolic variables (body weight, HbA_1c_, insulin, blood lipids, blood pressure), and (c) changes in women’s body composition as assessed by bioelectrical impedance analysis (BIA). Secondary measures will be taken at baseline visits, middle point, year 1, and 2, 3, and 4-year follow-up period.

**Table 1 Tab1:** Outcomes and timeline

Assessments	Screening visit	Baseline visit	Midpoint visit (26/27 weeks)	Year 1 visit	Year 2 visit (follow-up)	Year 3 visit (follow-up)	Year 4 visit (follow-up) endpoint
Lab tests							
OGTT test	X				X	X	X
Height, weight and blood pressure measurements	X	X	X	X	X	X	X
Bio-sample collection: buccal swab, saliva, and stool samples		X		X			X
BIA		X		X	X	X	X
Fasting blood draw		X	X	X	X	X	X
Questionnaires							
Demographics	X			X			
GDM and family history of diabetes	X						
Spouse and child health	X			X			
Lifestyle and dietary	X			X			
Diabetes awareness	X			X			
14-day e-Diary recording		X	X	X	X	X	X
SF-36		X	X	X	X	X	X
STAI		X	X	X	X	X	X
BDI-II		X	X	X	X	X	X
CERQ		X	X	X	X	X	X
MEQ		X	X	X	X	X	X
PSQI		X	X	X	X	X	X
SHS		X	X	X	X	X	X
HLQ		X	X	X	X	X	X
PSS-4		X	X	X	X	X	X
WHO-5		X	X	X	X	X	X
Child-related questionnaires							
BISQ-R-SF		X		X			
CSHQ		X		X			
StimQ toddler/preschool		X		X	X	X	X
ASQ-3		X		X	X	X	X
BRIEF-2		X		X	X	X	X
BASC-3-BESS Parent Form		X		X	X	X	X
Questionnaires administrated within the LvLUP App (intervention group only)							
PHQ-4		x	x				
IPAQ-SF		x	x				
MFFQ		x	x				

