*OGTT* 2-h 75 g oral glucose tolerance test, *BIA* Bioelectrical impedance analysis, *SF-36* short-form health survey, *STAI* The Stare-Trait Anxiety Inventory, *BDI-II* Beck Depression Inventory, *CERQ* Cognitive Emotion Regulation Questionnaire, *MEQ* Morningness-Eveningness Questionnaire, *PSQI* The Pittsburgh Sleep Quality Index, *SHS* Subjective Happiness Scale, *HLQ* Health Literacy Questionnaire, PSS-4 Perceived Stress Scale 4, *WHO-5* World Health Organization Wellbeing Index, *BISQ-R-SF* Brief Infant Sleep Questionnaire-Revised Short Form, *CSHQ* Children’s Sleep Habits Questionnaire, StimQ toddler/preschool Cognitive Home Environment Questionnaire, *ASQ-3* Ages & Stages Questionnaires-3, *BRIEF-2* Behaviour Rating Inventory of Execute Functions-2, *BASC-3-BESS Parent Form* Behavioral and Emotional Screening System, *PHQ-4* Patient Health Questionnaire, *IPAQ-SF* The International Physical Activity Questionnaire-Short Form, *MFFQ* Modified Food Frequency Questionnaire

Additionally, we will assess changes in women’s mental well-being by completing the following questionnaires at all study visits:

*Beck Depression Inventory* (BDI-II): A 21-item self-reported rating inventory using a 3-point Likert scale that measures symptoms and severity of depression, classified as follows: minimal (0–13); mild (14–19); moderate (20–28); and severe (29–63). The BDI-II internal consistency as measured by Cronbach’s alpha ranges from 0.87 to 0.93 [43].

*State-Trait Anxiety Inventory* (STAI): A 40-item self-report questionnaire using a 4-point Likert scale. The STAI measures two types of anxiety — state anxiety and trait anxiety, which are classified as no or low anxiety (20–37), moderate anxiety (38–44), and high anxiety (45–80). Internal consistency coefficients for the scale have ranged from 0.86 to 0.95 [44].

*Cognitive Emotion Regulation Questionnaire* (*CERQ*): A 36-item self-report measure designed to identify the cognitive emotion regulation strategies (or cognitive coping strategies) someone uses after having experienced adverse events or situations. It is commonly used to assess individual differences in the cognitive regulation of emotions in response to stressful, threatening, or traumatic life events. Internal consistency ranges from 0.72 and 0.83 [45].

*Subjective Happiness Scale (SHS):* A 4-item self-report measure to assess an individual’s overall happiness. Internal consistency ranges from 0.79 to 0.94 [46].

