## Statistical methods

### Statistical methods for primary and secondary outcomes {20a}

#### Analysis of aggregate intervention effects

The primary continuous outcome for the onset of diabetes will be analyzed with linear mixed models (LMM) with outcome measurement (at the three follow-up time points) as the dependent variable and based on the intention-to-treatment (ITT) principle.

Multiple linear regressions will determine the relationship between outcome measures and predictors, adjusting for potential confounders. Multiple linear regression analyses will estimate the effects between groups at the end point follow-up. Generalised estimating equations and mixed effect models will be used for longitudinal data analysis. A *p*-value of < 0.05 will be considered statistically significant. Correction for multiple tests will be performed. All statistical analyses will be conducted using the R program or STATA for Windows (Stata Corporation). The treatment effect within and between the two groups will be assessed using the Cohen *d* statistics [65].

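### Questionnaire scores are modelled with a single random effect per woman; if correlation between visits fades over 4 years, tests of late change reject too often and tests of early change too rarely

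*Protocol article*

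**What the plan says.** The section on non-adherence and missing data {20c} gives the model for the intention-to-treat efficacy analysis: "Total scores will be modelled using fixed effects of time, intervention group, interaction between time and intervention group, and a random effect of individual". This is the only place where the article names a random structure. It mentions no random slope, serial or unstructured residual covariance, or robust standard error. It does not say whether time is a linear term or a categorical visit factor.

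The scores are collected over a long and uneven schedule. Under Outcomes {12}: "we will assess changes in women’s mental well-being by completing the following questionnaires at all study visits". Table 1 shows six occasions for the women's questionnaires: baseline, 26/27 weeks, and years 1, 2, 3 and 4. The abstract names the early visits as the place to look for short-term effects: "Short-term aggregate effects will be assessed at 26/27 weeks (midpoint) and a 1-year visit, followed by a 2, 3, and 4-year follow-up period".

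The statistical methods section {20a} adds three things. A mixed model has "outcome measurement (at the three follow-up time points) as the dependent variable", without saying which three. A general sentence reads "Generalised estimating equations and mixed effect models will be used for longitudinal data analysis". The significance rule is a p-"value of < 0.05 will be considered statistically significant".

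**The concern.** A random intercept with independent residuals makes the correlation between any two visits of the same woman one constant. Repeated questionnaire scores may instead correlate less the further apart they are taken, because women drift along different paths. The model then estimates one within-woman variance averaged over short and long gaps. That average is too small for a contrast spanning 4 years and too large for one spanning 6 months.

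The nominal 5% level then holds for neither kind of contrast. A late difference could be declared because women's trajectories spread out, not because the arms differ. A real early effect, while the intervention is running, could be missed because its standard error is inflated. The planned correction for multiple tests acts on the p-values and cannot repair a wrong standard error.

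**Working it through.** **Inputs from the article.** Visits at 0, 0.5, 1, 2, 3 and 4 years (abstract; Table 1); 400 women allocated 1:1, so 200 per arm {16a}; nominal level 0.05 {20a}, taken as two-sided; the model in {20c}. A 20% dropout rate, borrowed from the censoring rate in the sample size section {14}, is used in a sensitivity run.

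**Inputs assumed.** All between-visit correlations, since the article gives none.

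The article gives no error rate for this model beyond the nominal 5%. Its sample size figures concern diabetes events and do not enter.

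**Formula (complete data, total variance 1).** Let V be the true 6 × 6 covariance and K = 6. The random-intercept model estimates the within-woman variance as s² = trace(PV)/(K − 1), where P is the within-woman centring matrix. This equals 1 minus the mean of the 15 pairwise correlations. For a contrast c over visits, compared between arms with no true difference:

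rejection rate = 2Φ(−1.96 × √(s²·c′c / c′Vc))

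Under constant correlation the ratio is 1 and the rate is 5%.

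**Worked case: correlation 0.8 per year of separation.** The gaps are 0.5 y (2 pairs), 1 y (4), 1.5 y (1), 2 y (3), 2.5 y (1), 3 y (2), 3.5 y (1) and 4 y (1). The correlations sum to 1.789 + 3.200 + 0.716 + 1.920 + 0.572 + 1.024 + 0.458 + 0.410 = 10.09, with mean 0.673, so s² = 0.327.

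- Year 4 − baseline: c′c = 2, c′Vc = 2(1 − 0.4096) = 1.181. Ratio 0.655/1.181 = 0.555; z = 1.96 × 0.745 = 1.46; rate 14.4%. The model's standard error is 0.745 of the true one.
- Year 1 − baseline: c′Vc = 2(1 − 0.8) = 0.400. Ratio 1.637; z = 2.51; rate 1.2%. The standard error is 1.28 times the true one.
- 6 months − baseline: c′Vc = 2(1 − 0.894) = 0.211. Ratio 3.10; z = 3.45; rate 0.1%. The standard error is 1.76 times the true one.
- Linear slope: c′c = 11.875, c′Vc = 11.22. Ratio 3.888/11.22 = 0.347; z = 1.15; rate 24.9%.

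**Across assumptions (six visits, closed form, nominal 5%).**

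| True correlation | Linear slope | Year 4 | Year 1 | 6 months |
|---|---|---|---|---|
| decay 0.9 per year | 26.6% | 16.0% | 0.9% | 0.0% |
| decay 0.8 | 24.9% | 14.4% | 1.2% | 0.1% |
| decay 0.5 | 18.8% | 10.0% | 2.4% | 0.3% |
| decay 0.8, 20% independent noise | 17.3% | 10.4% | 2.6% | 1.2% |
| 40% stable, 40% decaying at 0.8, 20% noise | 13.8% | 8.8% | 3.3% | 2.2% |
| 50% stable, 20% decaying at 0.6, 30% noise | 9.7% | 6.7% | 4.1% | 3.2% |

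The overall 5-df interaction test with categorical time gives 7.3 to 9.1% under pure decay and 5.2 to 6.7% under the mixed structures.

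**Fewer visits, linear time.** Years 2, 3 and 4 only: 5.9 to 10.5%. Visits at 0, 0.5 and 1 year: 5.7 to 10.7%. Baseline plus years 2, 3 and 4: 6.9 to 15.7%.

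**Simulation check.** The random-intercept model was fitted by REML to 1,500 simulated trials per scenario, with 0% / 20% dropout. Constant correlation 0.6 (control): linear 6.0% / 5.2%, categorical omnibus 4.9% / 5.5%. Decay 0.8: linear 25.3% / 26.5%, categorical 9.1% / 8.1%. A random-slope truth: linear 10.3% / 9.5%, categorical 5.6% / 5.5%. In a separate run of 500 trials with 20% dropout, sandwich errors by woman brought the rates back to 4.6 to 5.8%.

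**The case against.** The strongest reply has four parts.

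**Time coding and number of visits are open.** A reader might infer that the time-by-group test in general rejects 2 to 5 times too often. The article does not support that. The figure needs linear time over all six visits; the categorical omnibus test is only about 1.0 to 1.8 times nominal, and a three-visit model is milder than the six-visit slope. Nor are all intervals too narrow: the 6-month and year-1 contrasts err the other way. This stands, and it limits the claim.

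**Other methods are named.** {20a} mentions generalised estimating equations, and linear regression for the end-point comparison. Estimating equations with robust errors would avoid the problem, and a single-visit regression does not use the random-intercept covariance. But robust errors are not stated, and neither method is put in place of the model in {20c}. Having alternatives elsewhere does not correct the model that is written down.

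**The scores carry measurement error.** The quoted internal consistencies (0.87 to 0.93 for BDI-II, 0.72 for PSS-4, 0.64 to 0.83 for PSQI) suggest some noise. Reading 1 minus alpha as noise, a rough device, the linear six-visit rate falls to 11 to 22% and year 4 to 8 to 13%. This makes the top of the range less likely but does not remove the effect.

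**This is detail for an analysis plan.** Residual covariance often is, and an unseen plan may settle it. But {20c} goes beyond silence: it states the random structure, and a plan using another would depart from the published text.

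A reader might also extend the point to weight, HbA1c or diabetes onset. The sentence covers total scores only, so neither extension is supported.

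**Conclusion.** The point holds in a limited form. As written, the model for questionnaire scores is valid only if correlation is about equal for all gaps from 6 months to 4 years and residuals are independent. If correlation fades, its standard errors are too small for long-range change and too large for early change.

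Under the assumed structures, with six visits, the linear slope has a true level of about 10 to 27%, year 4 versus baseline about 7 to 16%, the overall categorical interaction about 5 to 9%, and the 6-month and year-1 contrasts about 0 to 4%. Three-visit linear models give about 6 to 11%. With near-constant correlation the problem disappears. The direction follows from the stated model once correlation fades; the size depends on correlations, time coding and a visit set that the article does not give.

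**What to change.** In {20c}, replace the single random effect with a repeated-measures model: visit as a categorical factor, arm, their interaction, and an unstructured within-woman covariance, with a random intercept and slope as the stated fallback if it does not converge. Alternatively, keep the random intercept but base all tests and intervals on cluster-robust standard errors by woman. In either case, list the visits that enter the model and name those at which the arms are compared.

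The cost is one or two sentences and no new data. An unstructured 6 × 6 covariance has 6 × 7 / 2 = 21 parameters, which about 400 women support. Intervals for long-range change will be wider than under the present model if correlation fades; that is the correct width.
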